**Fig 1 pone.0318922.g001:**
[figure not shown]
SPIRIT schedule of enrolment, interventions and assesments.

### Sample size

The sample calculation considered two independent samples with an estimated proportion of the ulcer healing rate of 75% for group 1, which will be treated with cell therapy, and 30% for group 2, which will be treated with hydrogel dressing. Assuming a test power of 80% and a significance level of 5% for a two-sided test, the sample was defined as 20 participants for group 1 and 20 participants for group 2 (1:1 allocation). This study was designed to be analyzed with intention to treat (ITT).

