### Sample size and Statistics

The results obtained through the primary and secondary outcomes will be tabulated weekly in an electronic spreadsheet by the study monitoring team. A sample of 40 participants is estimated. The data will initially be evaluated using descriptive statistics, with median/variance and/or mean/standard deviation analyses for quantitative variables and contingency table analyses for categorical/qualitative variables. To effectively recruit the intended number of participants, our strategy involves having study team members to actively engage with patients in the outpatient clinics and wards of HC-FMB. This direct approach will ensure that we connect with a wide range of patients who meet the criteria to participate in the study, maximizing our chances of success.

All data monitored in the study for Group 1 (cell therapy) and Group 2 (control) will be statistically compared. Quantitative data will be evaluated for their distribution (using the Shapiro-Wilk normality test) and compared using the T-test or the Wilcoxon test, depending on the type of distribution of the variables. For categorical variables, differences will be evaluated using Pearson’s Chi-square test or Fisher’s exact test. Bonferroni coefficient and multivariate analysis will also be used. In all statistical tests, the significance level of the independent variable will be set at 5% (p < 0.05).

Finally, the evaluation of the entire data set using multiple correspondence analysis (MCA) is proposed. For its application, each quantitative variable will be categorized according to the distribution quartiles of their respective data.

Categorical variables will be evaluated by means of Fisher’s exact test, continuous variables will be compared with non-parametric methods such as the Mann-Whitney test or U test, pairwise comparisons will be evaluated with the Wilcoxon test, multivariate analyses will be evaluated with regression analysis Cox curves, long-term clinical analyzes will be compiled into Kaplan Meir curves.

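### The stated 80% power with 20 per arm holds for an uncorrected Pearson chi-square test (82.3%) but not for Fisher's exact test (73.1%), which the statistics section names in one place as the only test for categorical variables

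*Protocol article*

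**What the plan says.** The Sample size section of the protocol article assumes "an estimated proportion of the ulcer healing rate of 75% for group 1" and "30% for group 2, which will be treated with hydrogel dressing". It continues: "Assuming a test power of 80% and a significance level of 5% for a two-sided test", and arrives at 20 participants in each group. The total is repeated under Sample size and Statistics: "A sample of 40 participants is estimated". Neither section names the test used for the calculation.

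Sample size and Statistics gives the test for categorical variables in two places. In the paragraph on comparing Group 1 with Group 2, "differences will be evaluated using Pearson’s Chi-square test or Fisher’s exact test". In the last paragraph on tests, "Categorical variables will be evaluated by means of Fisher’s exact test", with no alternative. Neither sentence is tied to the primary outcome, and nothing says which one prevails. Total epithelialization, the healing component of the primary efficacy outcome, is a yes/no variable, so both sentences apply to it.

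**The concern.** At 20 per arm, Fisher's exact test is clearly more conservative than the uncorrected chi-square test, so a sample size that suits one need not suit the other. If the Fisher-only sentence is followed, the chance of missing the assumed effect is about 27%, not the 20% that the protocol implies.

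The two sentences also leave the test for the main comparison open. Some plausible results are significant by one test and not by the other, and either p-value could be reported as following the protocol. In an open-label trial of 40 participants that choice should be settled before any outcome data are seen.

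**Working it through.** **Inputs.** All come from the Sample size section: p1 = 0.75, p2 = 0.30, two-sided α = 0.05, power 80%, n = 20 per arm. One binary outcome per participant is assumed, with no losses.

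**1. Reproduce the stated size.** The usual formula for two proportions with pooled variance under the null and no continuity correction is

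n = [1.960·√(2·p̄(1 − p̄)) + 0.842·√(p1(1 − p1) + p2(1 − p2))]² / (p1 − p2)², with p̄ = (0.75 + 0.30)/2 = 0.525.

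- First term: 1.960 × √0.49875 = 1.384.
- Second term: 0.842 × √(0.1875 + 0.21) = 0.842 × √0.3975 = 0.531.
- n = (1.384 + 0.531)² / 0.45² = 3.67 / 0.2025 = 18.1, so 19 per arm.

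The stated 20 is consistent with this calculation. The approximate power at 20 per arm is 84.1%. With the continuity correction, which approximates Fisher's test, the same formula gives 22.3, so 23 per arm.

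**2. Exact power at 20 per arm.** All 21 × 21 possible pairs of healed counts were enumerated. Each was weighted by Binomial(20, 0.75) × Binomial(20, 0.30), and the weights of the pairs with two-sided p < 0.05 were added. Maximum type I error is the largest rejection probability over all common healing rates.

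| Test | Power | Maximum type I error |
|---|---|---|
| Pearson, uncorrected | 82.3% | 5.3% |
| Boschloo, unconditional exact | 81.6% | 4.6% |
| Fisher's exact | 73.1% | 2.5% |

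**3. Size needed with Fisher.**

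| n per arm | Fisher power |
|---|---|
| 20 | 73.1% |
| 21 | 75.7% |
| 22 | 79.5% |
| 23 | 82.8% |

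Fisher first exceeds 80% at 23 per arm, 46 in total.

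**4. How often the choice matters.** At 20 per arm, every result significant by Fisher is also significant by uncorrected Pearson. The probability that they disagree under the design rates is therefore 82.3% − 73.1%, or 9.3% before rounding of the two powers. Two examples:

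| Healed, group 1 v group 2 | Fisher p | Pearson p |
|---|---|---|
| 14/20 v 7/20 | 0.056 | 0.027 |
| 15/20 v 8/20 | 0.054 | 0.025 |

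**The case against.** The strongest reply is that the sample size is correct for a test the protocol names. The Sample size section specifies no test, the standard formula reproduces its figure, and the sentence allowing Pearson stands in the paragraph on comparing the two groups. The convention often attached to such a sentence is to use Fisher only when an expected count is below 5. Under the design rates that would happen in about 0.03% of trials, so power would stay at 82.3%. The convention depends on the margins of the table, not on which p-value is smaller.

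Much of this stands. A reader might infer that the sample size contains an arithmetic error, or that the 80% is simply false. The documents do not support either reading, because 80% is delivered under one of the two instructions. A reader might also infer that the protocol lets the result pick the test. It does not prescribe that; it only fails to exclude it.

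What does not stand is that nothing needs changing. The small-count convention is not written in the protocol, and the Fisher-only sentence contradicts it. A rule for choosing a test may be left to an analysis plan that is not shown, but here the protocol itself gives two instructions that differ, and one does not fit its sample size.

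A further tempting step is to say that power is lower still because no allowance for losses is stated. If 10% in each arm were lost and counted as not healed (0.675 v 0.27), power would be 62% with Fisher and 73% with Pearson. Both the 10% and that counting rule are illustrative assumptions. The protocol gives no loss rate, and its missing-data text describes omission, interpolation and multiple imputation. An intention-to-treat analysis without an inflation factor is not a contradiction. This point does not rest on those figures.

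**Conclusion.** The point holds as an inconsistency between the sample size and one of the two test instructions. If the last paragraph on tests is followed, power is 73.1% against the stated 80%, a shortfall of about 7 percentage points. If uncorrected Pearson is used, the stated power is met at 82.3%. The documents do not say which applies to the primary outcome.

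The consequence is limited to power and to an open choice of test. Fisher is conservative here, so using it would not raise the false-positive rate. The figures assume the protocol's own healing rates, 20 analysed per arm and a single comparison of healing proportions at two-sided 5%.

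**What to change.** In Sample size and Statistics, name one test for the primary healing proportion and remove the conflicting sentence for that outcome. In Sample size, state the test to which the power refers. The options are:

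- **Uncorrected Pearson chi-square.** Already named in the protocol. Power 82.3% with 40 participants; maximum type I error 5.3%, slightly above nominal.
- **Boschloo's unconditional exact test.** New to the protocol. Power 81.6% with 40 participants; type I error at most 4.6%.
- **Fisher's exact test.** Either restate the power at 20 per arm as about 73%, or plan 23 per arm.

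The first two cost one sentence in each section and no extra participants. Keeping Fisher with restated power also needs only text changes; keeping it with at least 80% power costs six more participants (46 − 40). The change should be made before any outcome data are examined, including the partial analysis planned once at least five participants are in each group.

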### Randomization

Randomization will be prepared by a technician, using a random numerical table construction program available at http://stattrek.com/Tables/Random.aspx. Twenty positions will be drawn, with number 1 being fixed for Group 1 (cell therapy) and number 2 for Group 2 (control), randomly and consecutively. The envelope containing the randomization sequence will be held by an independent professional, the study team will not have access to the allocation order until time for adipose tissue collection.

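### The twenty-position list does not match 40 participants, no stated restriction secures 1:1, and the single-envelope wording does not secure concealment of later assignments

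*Protocol article*

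**What the plan says.** The Sample size section states that "the sample was defined as 20 participants for group 1 and 20 participants for group 2 (1:1 allocation". The Sample size and Statistics section repeats the total: "A sample of 40 participants is estimated". The Abstract also gives two groups of twenty.

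The Randomization section describes the list as follows: "Twenty positions will be drawn, with number 1 being fixed for Group 1 (cell therapy) and number 2 for Group 2 (control". It names no block, pairing or other restriction. A technician prepares the list. The sequence is kept in an envelope, in the singular, by an independent professional, and "the study team will not have access to the allocation order until time for adipose tissue collection".

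Three other places bear on this:

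- **Participant replacement** puts a substitute into the randomisation position of the participant who was excluded. It allows this up to the point before cell therapy is given.
- **The Abstract and the caption of Fig 2** describe adipose tissue collection for Group 1. The Group 2 description contains no such step.
- **Study design** calls the trial single-centre and open with blinded endpoints. The Blinding section has external evaluators read ulcer images by participant number.

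**The concern.** Two separate things are at stake.

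The first is the list itself. Twenty draws coded 1 or 2 do not supply 40 assignments, and independent draws do not fix the split at 20:20. Someone who has to build or audit the list from this paragraph must guess what was meant.

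The second, and more serious, is concealment. The paragraph withholds the allocation order, not an individual assignment, and it does so only up to tissue collection. In an open trial at one centre, the people who may learn the order also judge eligibility. Entry depends on judgements such as exhaustion of surgical options, optimised drug treatment, and re-evaluation after infection or an unstable condition. Ulcers from 1 to 20 cm² are eligible, and total epithelialisation is a primary efficacy outcome. Steering a few smaller ulcers towards one arm could therefore shift a comparison of 20 against 20. Blinded image reading protects the measurement of healing. It does not protect the decision about who enters which arm, and no analysis can repair that afterwards.

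**Working it through.** **1. Is 40 the planned number?**

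Inputs from Sample size: "an estimated proportion of the ulcer healing rate of 75% for group 1", "30% for group 2, which will be treated with hydrogel dressing", and "Assuming a test power of 80% and a significance level of 5% for a two-sided test".

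Pooled formula without continuity correction: n per arm = [1.96·√(2·p̄·q̄) + 0.8416·√(p₁q₁ + p₂q₂)]² / (p₁ − p₂)², with p̄ = 0.525.

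- 1.96·√0.49875 = 1.384
- 0.8416·√0.3975 = 0.531
- (1.384 + 0.531)² / 0.45² = 3.667 / 0.2025 = 18.1, so 19 per arm

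The stated 20 per group is reproduced to within one. The total of 40 is the design, and the figure of twenty in Randomization is what has to be reconciled with it.

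**2. What twenty positions would deliver**

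If each position is one assignment, 20/40 = 50% of the trial is covered. If the trial ended there with 10 per arm, power would be 52.5% (normal approximation) or 32.7% (Fisher's exact test).

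**3. Readings that reach 40**

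| Reading | Split of 40 | Consequence |
|---|---|---|
| (a) Independent draws of 1 or 2, extended to 40 | Not fixed | See step 4 |
| (b) Twenty consecutive pairs, each a 1 and a 2 in random order | Exactly 20:20 | In an open trial the second of each pair can be deduced: 20 of 40 assignments |
| (c) Twenty of 40 positions drawn for one group | Exactly 20:20 | A single block of 40 |

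The text does not say which is meant.

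**4. Size of imbalance under (a), with X ~ Binomial(40, ½)**

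- P(X = 20) = C(40,20)/2⁴⁰ = 0.125
- P(X ≤ 16 or X ≥ 24) = 0.268
- P(X ≤ 15 or X ≥ 25) = 0.154

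Power for 75% against 30% (normal approximation, Group 1 : Group 2):

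- 20:20 gives 84.1%
- 16:24 gives 82.5%
- 15:25 gives 81.7%

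The loss at 16:24 is 84.1 − 82.5 = 1.6 percentage points. By Fisher's exact test the figures are 73.1% at 20:20 and 74.8% at 16:24, so imbalance of this size does not lower power there either.

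**5. Concealment, from the text**

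- *Object disclosed:* the allocation order, from one envelope that contains the sequence. Release of one assignment at a time is not stated.
- *Time of disclosure:* adipose tissue collection. For Group 2 the text shows no such event, so the access point is undefined for 20 of the 40.
- *Replacement:* the Abstract puts 14–21 days of cell expansion between collection and application, and replacement is allowed until application. A participant excluded in that window has a known arm, and the substitute inherits it before enrolment. This holds even if assignments are released one by one.

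**The case against.** The strongest reply is that the paragraph can be read kindly. Twenty may mean twenty pairs, or twenty positions for one group. Either gives exactly 20:20 and agrees with the sample size. Independent draws would also be valid randomisation at little cost in power. A technician prepares the list, an independent professional holds it, and access is withheld until a defined step. This is a journal article that refers to a full protocol in S4 File, which is not shown, so numbering and opacity of envelopes may be settled there.

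Much of this stands. A reader might infer that balance fails. The documents do not support that: two of the three readings above give 20:20, so the split is only not secured. A reader might also infer that the envelope is opened at the first participant's collection, and that 39 of 40 assignments are then known. The text does not say first, and each participant's own collection is a fair reading. The 39 also presupposes a list of 40, whereas a literal list of twenty would leave at most 19 later assignments. Concealment is therefore not shown to fail, and up to the access point it is protected by independent custody.

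Brevity does not answer the rest. The article states a count that does not plainly match its own sample size, an access rule tied to a step described for one arm only, and a replacement rule that can pass on a known arm. These are stated rules, not omitted detail.

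**Conclusion.** The point holds in this form. The list as described does not match 40 participants, nothing stated secures the 1:1 split, and the custody and access wording does not secure concealment of later assignments.

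The balance part is minor. Under unrestricted draws, 20:20 occurs 12.5% of the time and 24:16 or worse 26.8%, but power falls by less than 2 percentage points at 16:24 under the planning rates. The concealment part carries the weight, because the trial is open and single-centre, entry involves judgement, and the resulting bias could not be undone. Its size cannot be calculated from the documents, since it depends on how the envelope is used in practice.

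The conclusion assumes that the full protocol does not already set out a 40-position list with single release. If it does, the article text should be brought into line with it.

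**What to change.** Rewrite the Randomization paragraph, and align Participant replacement with it:

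1. State a list of 40 positions, 20 per group, with a restriction that the study team cannot predict. Permuted blocks of varying size are one acceptable choice. Consecutive pairs are not, because the trial is open.
2. Keep the list with the independent holder already named. Release each assignment singly, by sequentially numbered, opaque, sealed envelopes or a call to the holder, after eligibility is confirmed and baseline data are recorded.
3. Define the release point in terms that apply to both groups, not by adipose tissue collection alone.
4. Give any replacement enrolled after an assignment has been disclosed the next unused assignment, not the disclosed position. Add reserve positions generated by the same rule so that the list does not run out.

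The cost is a protocol amendment, which Ethical and regulatory considerations requires to be submitted before implementation, and 40 envelopes or calls plus any reserves. The split may depart slightly from exact 20:20 after replacements, which step 4 of the working shows to matter little. The change should be in force before participants are randomised.

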#### Group 1.

Cell Therapy Treatment Group: Participants will receive expanded ASC treatment. The participant will undergo a surgical debridement procedure of the ulcer so that it is in its best condition (Visit 1). Subsequently, the participant will receive an ASC application via perilesional subcutaneous injections and a bio-dressing produced by the study team, also containing ASCs (the dressing containing ASC will remain in contact with the ulcer for 7 days in a single session). After removing the biological dressing, the participant will receive local care for the ulcer with a topical hydrogel dressing, dry gauze, and a crepe bandage, changed at least once a day.

#### Grupo 2.

Control Group: Participants will receive local ulcer care. The participant will undergo a surgical debridement procedure of the ulcer so that it is in its best condition (Visit 1). Subsequently, the participant will receive local care for the ulcer with a topical hydrogel dressing, dry gauze, and a crepe bandage, changed at least once a day.

### Recruitment

Participants will be recruited from June 1, 2025, to July 1, 2027. The data analysis should be finished by December 20, 2027. Eligible participants will be those who do not have an option for effective revascularization. They will be screened for inclusion in the study upon admission to the Clinical Hospital of the Faculty of Medicine, Botucatu, for treatment of peripheral artery disease (PAD) with chronic ulcers, or while receiving follow-up care at the Clinical Hospital Vascular Surgery’s Dressings Outpatient Clinic.

### Intervention

In the treatment group, the active component of this project’s cell therapy product is autologous ASCs [31–33], which will be expanded in the Laboratory (Cell Processing Center). The ASC will be made available to the patient in two presentations for use in a single treatment session: injectable solution and stable bio-dressing. The dosage planned for this clinical trial will be a single application of the products.

The procedure for applying the advanced cell therapy product proposed in this clinical trial will be carried out after locoregional (preferred) or general anesthesia, at the discretion of the anesthesiologist who will accompany the procedure, considering the participant’s clinical conditions, since the procedure cannot be performed without adequate analgesia. The application of injections and dressings will follow the rules of surgical procedures, carrying out antisepsis, placement of sterile drapes, manipulation of surgical materials, and opening of envelopes containing the products to be applied in a sterile manner.

Initial surgical cleaning and debridement will be carried out on the wound to make it ready to receive the treatment. Subcutaneous applications of 0.1 mL of the product consisting of the plasma solution and expanded autologous ASC will then be carried out every 1 cm from the edge of the ulcer (in the subcutaneous layer of the intact skin at the perimeter of the lesion), so that approximately 1x10^4^ ASCs are injected by puncture.

After the injections, the topical application of the stable bio-dressing will be carried out containing the ASCs on a membrane FIBRACOL™ Plus (Systagenix Brazil, dressing containing 90% collagen and 10% calcium alginate) with the same plasma solution containing cells in the proportion of 1x10^4^ ASCs per cm^2^ of the ulcer area to be covered (Fig 2). The dressing will be covered with rayon gauze (identifying the end of the primary dressing), the secondary dressing will be composed of a thin layer of moistened gauze with 0.9% saline, a layer with dry gauze, and, finally, a crepe bandage. Only the secondary dressing will be changed daily by the participant or their caregivers, according to instructions given by the study team. After 7 days, the ASCs absorption phase will be completed and the participant will return for reassessment of the ulcer, moving on to the phase in which the dressing will contain only hydrogel.

**Fig 2 pone.0318922.g002:**
[figure not shown]
Schematic representation of patient treatment in Group 1. Collection of adipose tissue, ASC expansion, dilution of ASC in plasma, preparation of bio dressing and application to the patient.

### Discontinuation criteria – participant withdraw

The participant has the right to withdraw from the study at any time, either of their own will or by decision of the researcher, due to safety issues or poor adherence to follow-up. If a participant communicates their withdrawal from the study or revokes their consent, this communication will be documented by the researcher and no data will be collected.

If, upon withdrawal from the study, the participant has an ongoing adverse event or unresolved clinical or laboratory abnormality, the researcher will offer follow-up until the event is resolved or stabilized.

The study monitoring team will maintain regular contact with participants through telephone calls to encourage them to attend their medical reassessment appointments. Additionally, the research team will be available to address any questions or concerns from participants at any time.

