### Discontinuation criteria – suspension of intervention

Participants will be withdrawn from the study if one of the following occurs:

Major amputation (ankle, leg, or thigh) of the treated limb.Loss of follow-up.Clinical worsening (at the discretion of the investigator).Active ulcer infection.Unfit conditions to be subjected to the cellular therapy procedure within one month after the set date for the procedure.

If a participant’s intervention is discontinued, they will be followed up and encouraged to return for scheduled visits.

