### Data collection plan

The study will be conducted at a single center, which will serve as the coordinating hub and be responsible for all stages of the RCT.

Verification and authenticity of the data quality entered into the electronic clinical record and printed documents will be carried out by the research team at our Clinical Research Unit (UPECLIN) according to the monitoring plan, during the execution and at the end of the clinical study.

To prevent data loss, we will develop standardized data collection forms and monitor the collected data regularly. Patients will be contacted frequently by telephone or social media, with updates often provided during these contacts. The appropriate clinical support will be offered to patients to minimize losses. Disease progression resulting in death or amputations will be defined as endpoints and will not be classified as data loss.

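### One no-data rule covers both leaving the study and revoking consent, and researcher withdrawal for poor attendance leaves outcome collection unstated, so obtainable outcomes (most clearly healing) may be given up in an open-label ITT trial

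*Protocol article*

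**What the plan says.** Under Discontinuation criteria – participant withdraw, a participant may leave "either of their own will or by decision of the researcher, due to safety issues or poor adherence to follow-up". If the participant communicates withdrawal from the study or revokes consent, "this communication will be documented by the researcher and no data will be collected". For someone with an unresolved adverse event or abnormality at that time, "the researcher will offer follow-up until the event is resolved or stabilized". The section ends with planned telephone calls to encourage attendance.

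The next section, on suspension of intervention, opens with "Participants will be withdrawn from the study if one of the following occurs" and lists five events. It closes with "If a participant’s intervention is discontinued, they will be followed up and encouraged to return for scheduled visits".

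Three other places bear on the point:
- Sample size: "This study was designed to be analyzed with intention to treat (ITT".
- Data collection plan: "Disease progression resulting in death or amputations will be defined as endpoints and will not be classified as data loss".
- Sample size and Statistics: a missing-data paragraph that includes multiple imputation.

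Study design describes an open trial with blinded endpoint assessment. Under Blinding, the evaluators and statisticians are the ones kept blind, not the treating team.

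**The concern.** Stopping visits and revoking consent to data use are different acts, and the article gives both the same consequence. A participant who says they are leaving the study, without objecting to a telephone call or a look at the hospital record, falls under the no-data rule.

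Treatment is a single session, so most later withdrawals will be from follow-up, not from treatment. Much of that loss is avoidable. The trial is run at one hospital, already telephones participants, and refers them to its own vascular clinic afterwards.

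The ground of poor attendance adds a second route. The person deciding knows the arm, and the article is silent on what happens to that participant's outcomes. Blinded scoring of photographs does not help here, because the evaluators do not control who remains to be photographed. Controls know they did not receive cells, so withdrawal may differ between arms, although the documents do not quantify this.

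**Working it through.** **1. Where each outcome stands after withdrawal**

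| Route out | What the article says about data |
|---|---|
| Participant revokes consent | None collected (proper) |
| Participant communicates withdrawal from the study | None collected (same rule) |
| Researcher withdraws for safety or poor attendance | Not stated |
| Listed event under suspension of intervention | Called withdrawn from the study, yet followed up |
| Death or amputation | Endpoint, not data loss; no statement that it is sought after withdrawal |
| Adverse event ongoing at withdrawal | Follow-up offered; no statement that it is recorded as trial data |

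Healing after a communicated withdrawal is the outcome most clearly lost. Limb and vital status are left unclear.

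**2. The planned sample size**

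Inputs from Sample size: p1 = 0.75, p2 = 0.30, power 80%, two-sided 5%, 20 per arm. The mean rate is p = 0.525.

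n = [1.960 × √(2 × 0.525 × 0.475) + 0.842 × √(0.75 × 0.25 + 0.30 × 0.70)]² / 0.45²
= [1.960 × 0.706 + 0.842 × 0.630]² / 0.2025 = 18.1, so 19 per arm.

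The stated 20 is therefore reproduced to within one. There is no error in it, and the margin for lost outcomes is one participant per arm.

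Power with n evaluable per arm = Φ[(0.45√n − 1.960 × 0.706) / 0.630]: 84.0% at 20, 82.0% at 19, 79.8% at 18, 77.3% at 17. Exact power for Fisher's test, which the article also names, is lower: 73.1% at 20 and 67.9% at 17.

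**3. What a few lost outcomes could do**

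The article gives no withdrawal rate. Assume two or three lost per arm (10% or 15%), with the planned rates among those observed, rounded to whole participants. The p-values are two-sided Fisher.

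| | Three lost per arm | Two lost per arm |
|---|---|---|
| Observed only | 13/17 v 5/17, p = 0.015 | 14/18 v 5/18, p = 0.007 |
| Unfavourable bound (lost cell-therapy participants unhealed, lost controls healed) | 13/20 v 8/20, 25 points, p = 0.20 | 14/20 v 7/20, 35 points, p = 0.056 |
| Favourable bound (the reverse) | 16/20 v 5/20, 55 points, p = 0.001 | 16/20 v 5/20, 55 points, p = 0.001 |
| All lost counted as not healed | 13/20 v 5/20, 40 points, p = 0.025 | 14/20 v 5/20, 45 points, p = 0.010 |

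Each unknown participant is worth 1/20 = 5 percentage points of an arm.

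**The case against.** A reader might infer that any withdrawal, including removal by the researcher, loses limb status, death and healing by rule. The text does not support that, for two reasons:
- The no-data sentence attaches to a participant who communicates withdrawal or revokes consent. It is not attached to a researcher's decision, where the article is simply silent.
- The Data collection plan makes death and amputation endpoints and not data loss, so they cannot be called lost by rule. That sentence classifies a known event, however, and does not say that events after withdrawal will be looked for.

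A reader might also infer flat contradictions with the neighbouring text. These are weaker than they look. Offered follow-up of an adverse event can be read as clinical care. Following those whose intervention stopped, while ceasing collection from those who leave the study, can be read as a coherent distinction. It is blurred because the suspension section also calls its participants withdrawn from the study. Intention to treat fixes who is analysed and in which arm, and does not by itself oblige collection from people who have left.

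Three further objections have some force:
- The text speaks of leaving the study, not of declining a visit, and calls are planned to encourage attendance. But no intermediate status is offered to someone who wants to stop visits only.
- A condensed article may leave graded withdrawal to the full protocol. Here, though, the article states the rule, and the rule itself is the difficulty.
- Multiple imputation is provided for. It does not recover outcomes that the plan chose not to collect.

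Finally, the bounds are extreme. Any trial of this size with missing outcomes would show wide ones, and counting all missing as not healed leaves both scenarios significant.

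**Conclusion.** The point holds in a limited form. One rule covers two kinds of withdrawal that should be handled differently, and poor attendance is a ground for withdrawal by an unblinded researcher with the consequence for data unstated. Followed as written, this forgoes obtainable outcomes in an open-label trial designed for intention to treat. Healing is clearly affected; ascertainment of limb and vital status after withdrawal is left open.

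The size depends on an assumed two or three losses per arm. Under the most unfavourable pattern, significance would be lost (p = 0.056 or 0.20); under non-healer imputation it would not. The figures show that a handful of outcomes could matter, not that the result would be biased by a given amount. Ending collection after revoked consent is not criticised, and no numerical error is alleged. The change is worth making because it is cheap and protects the primary outcome.

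**What to change.** In Discontinuation criteria – participant withdraw, distinguish two levels:
- (a) The participant stops study visits but does not revoke consent to data use. Vital status, any amputation, serious adverse events and, if the participant agrees, ulcer status continue to be recorded by telephone or from the hospital record up to the final assessment.
- (b) The participant revokes consent. New collection stops and data already recorded are kept.

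Remove poor attendance as a ground for the researcher to withdraw someone from the study, and record missed visits as missed. For withdrawal by the researcher on safety grounds, state that outcome collection continues as in (a) unless consent is revoked. State whether information from the offered adverse-event follow-up is entered as trial data.

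Reconcile this section with the intention-to-treat statement, the suspension-of-intervention section and the endpoint sentence in the Data collection plan, including that death and amputation are sought after withdrawal at level (a).

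The cost is a minor ethics amendment, one sentence in the consent form, and a telephone or record check for each participant who stops visits, using contacts already planned.
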